## Abstract

**Background:**

A pilot project cardiovascular prevention was implemented in Sandwell (West Midlands, UK). This used electronic primary care records to identify untreated patients at high risk of cardiovascular disease then invited these high risk patients for assessment by a nurse in their own general practice. Those found to be eligible for treatment were offered treatment. During the pilot a higher proportion of high risk patients were started on treatment in the intervention practices than in control practices. Following the apparent success of the prevention project, it was intended to extend the service to all practices across the Sandwell area. However the pilot project was not a robust evaluation. There was a need for an efficient evaluation that would not disrupt the planned rollout of the project.

**Methods/design:**

Project nurses will sequentially implement targeted cardiovascular case finding in a phased way across all general practices, with the sequence of general practices determined randomly. This is a stepped wedge randomised controlled trial design. The target population is patients aged 35 to 74, without diabetes or cardiovascular disease whose ten-year cardiovascular risk, (determined from data in their electronic records) is ≥20%. The primary outcome is the number of high risk patients started on treatment, because these data could be efficiently obtained from electronic primary care records. From this we can determine the effects of the case finding programme on the proportion of high risk patients started on treatment in practices before and after implementation of targeted case finding. Cost-effectiveness will be modelled from the predicted effects of treatments on cardiovascular events and associated health service costs. Alongside the implementation it is intended to interview clinical staff and patients who participated in the programme in order to determine acceptability to patients and clinicians. Practical considerations meant that 26 practices in Sandwell could be randomised, including about 6,250 patients at high risk of cardiovascular disease. This gives sufficient power for evaluation.

**Discussion:**

It is possible to design a stepped wedge randomised controlled trial using routine data to determine the primary outcome to evaluate implementation of a cardiovascular prevention programme.

## Background

Cardiovascular disease (CVD) remains the UK’s largest cause of morbidity and mortality. There is overwhelming evidence that drug treatment to lower blood pressure and lipid levels reduce the incidence of and mortality from CVD. Under UK guidelines, statins are recommended for all high-risk patients and antihypertensive drugs for those high risk patients if their blood pressure is ≥140/90 mm Hg
[1-4]. They also recommend that patients with familial hypercholesterolaemia are prescribed statins and those whose blood pressure ≥160/100 mm Hg are prescribed antihypertensives, irrespective of their risk status
[1,3,5]. The guidelines define high risk as either the presence of atherosclerotic disease or ≥20% predicted ten-year cumulative risk of coronary heart disease or stroke, using the Framingham equations.
[5] This means that all those at ≥20% ten-year CVD risk are eligible for statin treatment and many are eligible for both statin and antihypertensive treatments. Some guidelines also recommend that individuals at ≥20% ten-year CVD risk should be offered aspirin
[3,4]. However, the recommendation is controversial as the risk benefit ratio in patients taking other preventive treatments is only marginally favourable
[6].

Historically in the UK there have not been systematic attempts to identify and offer CVD prevention and most primary prevention of CVD has been undertaken when patients are identified opportunistically in primary care. However there may be weaknesses with this approach. GPs do not always follow guidelines in routine clinical practice
[7]. They may not fully recognise the clinical importance of statin prescribing and when eligible patients consult, physicians commonly delay prescribing decisions until the next visit
[8,9]. There is also confusion about which patients are eligible for treatment. In New Zealand, where risk based hypertension guidelines were first adopted, clinicians reported they would treat low risk younger adults at lower blood pressures than high risk older adults
[10]. When deciding whether to prescribe, GPs also seem to give greater weight to individual risk factor values than global risk
[11]. In opportunistic screening CVD risk calculation may also not be carried out, it may be done incorrectly and it often varies from one physician to another
[12-15]. The opportunistic strategy therefore may not be sufficient and in the UK, many eligible individuals remain untreated. In 2009, 29% of adults were hypertensive of whom 51% were untreated and the figures have changed little since 2005
[16].

Recently, the NHS announced a programme of NHS Health Checks, to be offered to all adults aged 40 to 74 as part of a five year rolling programme to screen people for CVD and diabetes and offer lifestyle and preventative advice
[17]. Economic modelling suggested that universal screening, such as that implemented under the NHS health checks, would be cost effective
[18]. However, the modelling did not explicitly compare a strategy of universal screening of all those in the selected age range with case finding targeted at those most likely to benefit. Furthermore, cost-effectiveness modelling studies indicate that a strategy of prioritising untreated patients for assessment on the basis of their estimated ten-year CVD risk should, in theory, be the most efficient prevention strategy for untreated patients
[19,20]. This finding has further support from a subsequent modelling study using a different multivariable risk prediction equation
[21].

Economic modeling studies therefore suggest that targeted, rather than universal, screening approaches could be cost-effective. However, since it was uncertain whether results of modeling studies would be realised in actual practice, we are therefore undertaking a controlled evaluation of a targeted versus opertunistic screening approach for cardiovascular risk.

This paper presents the protocol for a stepped wedged cluster randomised controlled trial that aims to quantify the benefits of targeted case finding of patients at high risk of CVD over opportunistic assessment and overcome the challenges of evaluation. The primary hypothesis is that targeted case finding will increase the rate at which high risk patients are started on treatment. A pilot study, reported in full elsewhere, was undertaken to determine feasibility and for completeness the findings from this pilot study are briefly summarised before the methodology for the full study are presented
[22].

### Pilot study for targeted case finding

In 2005–6 a pilot project of case finding for untreated high risk patients was implemented in six general practices in the area covered by Sandwell Primary Care Trust in the West Midlands, England. In six general practices cardiovascular risk factor data were extracted from electronic primary care records of all untreated patients aged 35 to 74 and high risk patients were identified from information in their records. Over the course of one year, in four of the six practices, high risk patients were sent invitation letters offering assessment by the project nurse in their own general practice by a project nurse and if, they were confirmed to be eligible for treatment were referred to their GP for treatment. Over the same period, two control general practices were provided with an equivalent list identifying their high risk patients but elected to assess patients opportunistically.

Twice as many high-risk patients had their CVD risk factors assessed in the intervention than control practices (62% v 28%). Four fifths of those patients who were assessed, were confirmed to be high risk. Three times more eligible high-risk patients were started on preventive treatment in the intervention than in the control practices (41% v 13%)
[22].

Results from the Sandwell pilot suggested that it is feasible to implement a programme of targeted case finding and that this might have similar advantages over opportunistic screening to those estimated from modelling studies
[19,20]. A further study, in Solihull Care Trust, also demonstrated support for feasibility of implementation of the intervention using a prescribing advisor instead of a nurse.

However, it was not known if these results could be replicated across a larger number of practices and the small and non-randomised nature of the evaluation means that the apparent increase in patients started on treatment could reflect systematic differences between the practices rather than effects of the intervention. There was also little information on the experience of the case finding programme from the perspective of patients or of practice staff.

### Challenges of implementation and evaluation

The evidence of effectiveness of the intervention from the pilot study, although encouraging, is limited and so it is important to undertake a robust evaluation of the programme. If targeted case finding could be demonstrated to be more effective than opportunistic assessment it could be advocated more widely across primary care systems. However, both implementation and evaluation presented a number of challenges. First, an efficient method must be found to identify untreated high risk patients for invitation. Second, a practical plan was needed for implementation across a large number of general practices given limited resources for implementation. Third, a methodology was needed to evaluate the effects of targeted case finding given the fact that in both Sandwell and Solihull the case-finding programmes were to be implemented in all practices at the same time. Fourth, an efficient means of data collection needed to be identified.

### Implementation and stepped wedge evaluation

Within Sandwell Primary Care Trust there was support to continue and expand the targeted case finding project to include all its practices and within Solihull Care Trust there was support to expand the project to include all practices in the northern part of the care trust. However the number of project nurses/prescribing advisors available to implement the case finding was limited and it was therefore not possible to offer targeted case finding to all practices concurrently. It was therefore planned that the project nurses/prescribing advisors would sequentially implement the target case finding in a phased way across all general practices. Because the unit of intervention for the case finding programme was a general practice, it was neither practical nor acceptable to randomly allocate individual patients to invitation to a case finding programme or usual care. However the phased intervention across general practices provided an opportunity to evaluate the effects of the case finding programme on the proportion of high risk patients started on treatment in practices before and after implementation of targeted case finding. If the order in which case finding was implemented in practices could be randomised this would form the basis of a stepped wedged cluster randomised controlled trial
[23].

A stepped wedge cluster randomised controlled trial is a study design that has been used to evaluate interventions in health care, social policy and education
[24]. They have mainly been used to evaluate routine implementation and the earliest published example involved roll out of Hepatitis B immunisation across regions of Gambia
[25]. In this type of trial the intervention is implemented in a number of clusters but the order in which clusters receive the intervention is random (Figure
1). At the end of the trial all clusters will have received the intervention. Outcome data are collected at each step; in other words at each time point where a new cluster receives the intervention. Analysis therefore compares data points in the control section of the wedge (not exposed to the intervention) with those in the intervention section (exposed to the intervention).

**Figure 1 F1:**
[figure not shown]
Stepped wedge trial design with different steps of different durations.

## Methods/design

### Practice recruitment

By 2008 of 65 practices in Sandwell Primary Care Trust, case finding had already been completed in 12 (six as part of the pilot project); in a further 25, case finding had started or a start date had already been agreed; two practices did not have available consultation rooms in the practice building, leaving 26 practices for randomisation. The total population registered with these practices was approximately 125,000 and from the pilot study it was anticipated that 5% (about 6,250) would be untreated high risk patients.

There were six practices in Solihull Care Trust in whom the targeted case finding programme could be implemented. The total population registered in these practices was 18,938 and it was anticipated that 945 (5%) would be untreated high risk patients.

Therefore overall 32 practices, representing 32 separate clusters, were included in the study with a combined estimated 7,247 untreated people at high risk of CVD.

### Randomisation

Randomisation was stratified by primary care trust. In Sandwell PCT, after discussion with the case finding programme manager, it was agreed that 11 practices were a higher priority for the case finding intervention and the remaining 15 practices were a lower priority. It was therefore decided to stratify the practices into two groups for randomisation: early intervention and late intervention. A table of random numbers was generated to determine the order in which practices should receive the project nurse led intervention in the early intervention group and a second table for practices in the late intervention group.

The six practices in Solihull were of different characteristics, two were single handed and two were located very near each other and served similar populations. They were therefore stratified into three pairs (two single handed, two similar location and two remaining practices) for randomisation. A table of random numbers was generated to determine which of each pair should have the intervention first and which second.

### Inclusion criteria

All patients aged 35 to 74 who were not currently on the CVD or diabetic registers and who were not currently receiving antihypertensive or statin treatment (no prescription within 90 days) were included in the programme. From this were selected all those whose estimated ten-year CVD risk ≥20%.

Practice software systems were used to identify patients with a ten-year CVD risk ≥20%. In Sandwell PCT all practices subscribe to Clinical Manager software manufactured by MSDi
[26]. This software produces lists of patients meeting pre-specified criteria (e.g. diabetic patients due for a blood pressure measurement). The manufacturers incorporated an additional module into the software to calculate ten-year CVD risk for all untreated patients without CVD using the Framingham risk equations
[27]. The following method was used to deal with missing risk factor data. If smoking status was missing the patient was assumed to be a non smoker; if blood pressure or cholesterol values were missing a default value was used, based on the average for an untreated person of that age, sex, smoking status and diabetic status. This followed a previously described method
[28]. In Sandwell PCT this allowed every practice to produce a list of untreated patients at ≥20% ten-year CVD risk (high risk patients).

In Solihull PCT practice data was extracted using the search facility in the electronic patient records and exported to an Excel spreadsheet. Ten year CVD risk (high risk patients) was calculated in the spreadsheet using the same method and patients at ≥20% ten-year CVD risk (high risk patients) were identified for the practices.

### Exclusion criteria

Participating practices reviewed the list of high risk patients identified and excluded those who had died, moved practice and or who the GP judged were unsuitable for CVD prevention (e.g. those with a terminal illness).

### Intervention

The intervention in Sandwell was delivered by project nurses trained in the management of either diabetes or coronary heart disease. In Solihull prescribing advisors, trained pharmacists who were licensed to prescribe, delivered the intervention.

In the intervention practices the project nurse (Sandwell) or prescribing advisor (Solihull) arranged for a letter along with an information sheet about the case finding project to be sent from the GP inviting patients for cardiovascular assessment. The letter specifically mentioned that patients might be offered lifestyle advice and medication ( Additional file
1 and Additional file
2). The patient was given the time and date of an appointment for their CVD assessment and asked to reschedule if this was unsuitable. If they did not attend or reschedule the appointment two further attempts were made to contact patients either by letter or telephone.

Patients who attended underwent a full cardiovascular risk factor assessment, including enquiry about smoking, measurement of blood pressure, blood tests for fasting glucose, total cholesterol and HDL cholesterol. Each patient’s ten-year CVD risk was calculated using the Framingham equation as recommended in UK guidelines based on their measured risk factors and their eligibility for treatment was determined
[2,3]. If they were eligible for antihypertensive or statin treatment the project nurse/prescribing advisor discussed the risks and benefits of treatment with the patient and the general practitioner was informed so that treatment could be initiated. If appropriate the patient could also be referred to local smoking cessation services, for advice on physical activity or for dietary advice about weight loss.

Patients at highest risk were invited first followed by those at next highest risk until all high-risk patients (≥20% ten-year CVD risk) had been invited. The project nurse (or prescribing advisor) then repeated the process in the next practice in a sequence determined by the randomisation. Because the practices varied in size this meant that the number of weeks spent at each practice would be expected to vary from one practice to another. It was anticipated that it would take about 18 months to complete the implementation of targeted case-finding in all Sandwell practices and about 12 months in Solihull practices.

### Primary outcomes

Since there is good evidence for the effectiveness of CVD prevention, it is reasonable to use uptake of treatment as evidence of effectiveness. Prescriptions of antihypertensive drugs or statins are recorded in electronic primary care records, therefore routine data could be used to assess outcomes.

The primary outcome is the number of high-risk patients started on at least one preventive treatment: an antihypertensive drug or a statin. Antihypertensive drugs and statins are defined by the chapter codes in the British National Formulary
[29].

Secondary outcomes include the number of patients who have cardiovascular risk factors assessed (blood pressure, lipid levels); the number of patients referred to services for lifestyle advice (smoking cessation services, advice on physical activity, dietetic advice on weigh loss); changes cardiovascular risk factors (blood pressure, lipid levels); cardiovascular events (new diagnoses of angina, MI, TIA or stroke).

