The primary aim of the study is to evaluate whether there is a difference in proportion of eligible patients on the relevant prescription medication before and after the practice was exposed to the intervention. In statistical terms this null-hypothesis (no difference) can be tested using a mixed logistic regression model with binary outcome (prescription of the appropriate medication). Important independent variables to consider are the clustering effect (i.e. effect of GP practice), calendar time effect (since the intervention is sequentially rolled-out) and an indicator of intervention exposure for each practice at each time point; in an to adjustment for other characteristics [4]. These models will be fitted using population averaged models using GEE methods in STATA, allowing for clustering and adjusting for individual level covariates and any cluster level covariates where available. Population averaged models as opposed to random effects models (also known as marginal models) will be used as within the framework of cluster randomised trials, random effects models both lack appropriate interpretation and might be biased
[31]. The covariates to be included in the adjustment will be pre-specified and will include practice size and patient level characteristics (age, sex, diabetic status, smoking status, blood pressure, total cholesterol and HDL cholesterol); GP practice will be included as a random effect; time point as a fixed effect; and exposure or non-exposure as the main intervention effect. Null hypotheses for secondary outcomes take a similar form to that for the primary outcome. Analysis of the secondary outcomes will take a similar form to that described for the primary outcome.

The primary outcome will be considered significant at the 5% level and so 95% confidence intervals (CIs) reported; whereas secondary outcomes will be deemed significant at the 1% level (and so 99% CIs reported). This difference in levels of significance, give more weight to the primary outcomes. Analysis will be stratified by primary care trust: the analysis of the project nurse led intervention in Sandwell and the prescribing advisor led intervention in Solihull will be carried out separately.

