### Ethical approval

Advice on the need for ethical approval was sought from the National Research Ethics Service. Implementation of the targeted case-finding programme was being rolled out as rapidly as was practical. The order in which the implementation was being carried out in each practice had been determined in advance by randomisation. No additional investigations or measurements were being undertaken and no patient identifiable data would leave the NHS. We were therefore advised that this did not need ethical approval as it was evaluation of a service development [ Additional file
3].

Although interviews with patients and clinical staff for the qualitative evaluation could also be considered as part of the service evaluation we sought and obtained ethical approval from the University of Birmingham ethics committee for this part of the study [ Additional file
4]. Information sheets and consent forms were provided for interview participants who were clinical staff or patients [ Additional file
5, Additional file
6, Additional file
7 and Additional file
8].

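### Change in blood pressure and lipids is to be tested by exposure, but it is seen only in measured patients, and the intervention strongly influences who is measured

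*Protocol article*

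**What the plan says.** The protocol article, under Primary outcomes, names as secondary outcomes both "the number of patients who have cardiovascular risk factors assessed (blood pressure, lipid levels") and "changes cardiovascular risk factors (blood pressure, lipid levels").

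Under Analysis it states: "Analysis of the secondary outcomes will take a similar form to that described for the primary outcome". The primary model has exposure or non-exposure as the main effect and time point as a fixed effect. It allows for clustering by practice and adjusts for, among other things, blood pressure, total cholesterol and HDL cholesterol. Secondary outcomes are judged at the 1% level with 99% confidence intervals.

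The data are one extract of electronic records at the end of the study (Follow up and data collection). The Ethical approval section says: "No additional investigations or measurements were being undertaken". Under Intervention: "Patients who attended underwent a full cardiovascular risk factor assessment", and "Patients at highest risk were invited first followed by those at next highest risk". The pilot section reports: "Twice as many high-risk patients had their CVD risk factors assessed in the intervention than control practices (62% v 28"%).

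For building the list of high-risk patients, Inclusion criteria says: "if blood pressure or cholesterol values were missing a default value was used".

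**The concern.** A prescription is recorded whether or not the patient was assessed, so the primary outcome can be determined for every listed patient. A change in blood pressure or cholesterol cannot: it needs a baseline value and a later one, and no study measurement fills the gaps. In exposed time the later value often exists because the patient was invited. In unexposed time it exists because the patient consulted for some reason.

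The plan itself expects exposure to alter who is measured, since the number assessed is an outcome in its own right. Carrying the primary model over to change therefore conditions on something that the intervention affects. Randomising the order of practices makes all listed patients comparable, but not the measured ones. What is at stake is a result at the 1% level, read as an effect of case finding on risk factors, that partly reflects which patients have a reading. The limitations in the Discussion do not mention this.

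**Working it through.** **No figure to reproduce.** The protocol gives no effect size, SD or power for this outcome. The one related figure is consistent: 0.62 / 0.28 = 2.21, in line with twice as many assessed. At those rates 38% of exposed and 72% of unexposed patients would have no assessment.

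**Inputs.** From the document: 62% and 28% measured, and adjustment for blood pressure. Assumed, for systolic pressure: true between-patient SD 12 mmHg, measurement-error SD 10, drift in true pressure between readings SD 0 or 8, exposed patients measured at random, and unexposed measurement logistic with slope b = 0.25 or 0.5 per SD of the variable that drives it. No patient has a true effect.

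**Formulas.** Differences are exposed minus unexposed. To first order, measuring a fraction p with slope b shifts the driving variable in those measured by b(1 − p) SD. With p = 0.28 this is 0.72b: 0.18 SD at b = 0.25 and 0.36 SD at b = 0.5. The variance of a recorded baseline is 12² + 10² = 244 (SD 15.6). The regression of a later reading on baseline has slope 144/244 = 0.59, leaving 0.41 unexplained.

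- *Selection on the recorded baseline.* Unadjusted: 0.41 × 15.6 × 0.18 = 1.2 mmHg, and 2.3 at b = 0.5. Adjusted: 0, because the driver is the covariate.
- *Selection on underlying pressure.* Unadjusted: 0. Adjusted: −0.41 × 12 × 0.18 = −0.9, and −1.8 at b = 0.5.
- *Selection on current pressure, drift SD 8.* Current variance is 144 + 64 = 208 (SD 14.4). Its shift is 0.18 × 14.4 = 2.6, and the baseline shift is 2.6 × 144/208 = 1.8. Adjusted: −(2.6 − 0.59 × 1.8) = −1.5, and −3.1 at b = 0.5.

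**Simulation** (2 million patients per condition), mmHg:

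| Unexposed measurement depends on | Slope | Unadjusted | Baseline-adjusted |
|---|---|---|---|
| Recorded baseline | 0.25 / 0.5 | 1.1 / 2.2 | 0.0 / 0.0 |
| Underlying pressure | 0.25 / 0.5 | 0.0 / 0.0 | −0.9 / −1.7 |
| Current pressure, drift SD 8 | 0.25 / 0.5 | −0.8 / −1.5 | −1.5 / −2.9 |

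With negative slopes the signs reverse and the sizes are the same. The two methods agree to within 0.2 mmHg.

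**Reading.** Adjustment cures the first case. In the second it introduces a bias that the raw comparison lacks, and in the third it enlarges one. Neither analysis is safe in all three, and the records cannot show which case applies.

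**If both conditions are selective.** A normal selection model, without covariates, gives a bias of SD × [ρ_exp λ(0.62) − ρ_unexp λ(0.28)], where λ(0.62) = 0.614 and λ(0.28) = 1.202. With equal correlations of 0.1 to 0.3 the result is −0.06 to −0.18 SD. Equal selection in the two conditions does not cancel, because different fractions are measured.

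**The case against.** The strongest objection is that the plan adjusts for blood pressure and cholesterol, and baseline is the natural reading of those covariates. This stands for selection on a recorded baseline: the adjusted difference is then zero. A reader might take the unadjusted 1.1 to 2.2 mmHg as the bias of the planned analysis. The document does not support that, because the planned analysis is adjusted. It does not stand for selection on underlying or current pressure, or on reasons for consulting that the covariates do not capture.

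A second objection is that the article fixes only a similar form of analysis, so the definition of change, the measurement window and the missing-data method belong in an analysis plan. That is fair, and their absence is not the criticism. The criticism is of what the article does fix: change as an outcome, exposure as the comparison, and a significance claim at 1%.

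Two stronger readings should be resisted:

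- A reader might infer that default values will serve as baselines, so that some changes are measured minus assumed. The article describes defaults only for calculating risk and building the list, and outcome data come from a separate extract of dated records.
- A reader might say that the intervention decides who is measured. Attendance is the patient's choice, and 28% of control patients in the pilot were assessed without it.

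**Conclusion.** The concern holds as a risk of selection bias in one secondary outcome. Under the assumptions above and no true effect, the baseline-adjusted spurious difference in systolic pressure is about 0.9 to 3.0 mmHg, and it could favour either condition. The document gives neither the SDs nor the strength of selection, so size and direction cannot be fixed from it. The bias is zero if measurement is unrelated to the value once the covariates are allowed for, or if the selection in the two conditions happens to cancel. The same reasoning applies to lipids, for which no size was calculated. The illustration leaves out clustering and calendar time.

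A reader might extend the point to the primary outcome. That would be wrong, because prescriptions are recorded whether or not a patient was assessed.

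**What to change.** - Make no 1%-level significance claim on change in blood pressure or lipids, and label these results exploratory.
- Report them in patients with an actually recorded baseline and a later recorded value, beside the proportion measured in exposed and unexposed time.
- Keep the number of patients assessed as the tested outcome. It is defined for every listed patient.
- If a comparison by exposure is kept, weight it by the modelled probability of being measured, or use another stated missing-data method. Add a sensitivity analysis in either case: weights built from recorded covariates share the limit of the adjustment and cannot remove selection on unrecorded current values.
- State that the default values used for the risk list are not used as baselines for change.

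The cost is wording. Dated blood pressure and cholesterol values are already among the extracted fields. The trial gives up a formal significance claim on one secondary outcome.
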